## Abstract

•Australian-first school-led trial targets personality risk factors for psychopathology.•Examines effectiveness for substance use, internalising, externalising outcomes.•Seeks evidence for feasible and scalable delivery of *Preventure* for schools.•Adds to limited research on effectiveness of prevention programs rather than efficacy.

Australian-first school-led trial targets personality risk factors for psychopathology.

Examines effectiveness for substance use, internalising, externalising outcomes.

Seeks evidence for feasible and scalable delivery of *Preventure* for schools.

Adds to limited research on effectiveness of prevention programs rather than efficacy.

## Introduction

1

Mental disorders are the leading cause of disability for young people worldwide, accounting for 25% of all years lived with disability and over 1.3 million years of life lost (Vigo et al., 2016, Erskine et al., 2015). Mental disorders have significant social and economic impacts, largely attributable to their high prevalence, early age of onset, and chronic, disabling course. The most common mental disorders among adolescents in Australia are attention deficit hyperactivity disorder, anxiety disorders, depressive disorders, and conduct disorder (Lawrence et al., 2015). To make a significant impact on these disorders at a population level, it is imperative that public health shifts focus to prevention (Pine and Fox, 2015), rather than focusing on treating individuals with entrenched disorders.

Problematic alcohol use is also an issue of vital importance in Australia. While trends over the last 20 years show that Australian adolescents are delaying their onset of alcohol use, and are less likely to smoke tobacco and use illicit drugs, drinking at risky levels remains high (Australian Institute of Health and Welfare, 2019). Harmful alcohol use (exceeding the National Health and Medical Research Council guidelines (National Health and Medical Research Council, 2009) is a major health issue, associated with increased risk of chronic disease, injury and premature death (Australian Institute of Health and Welfare, 2019). Alcohol use is especially risky for adolescents given the impact on the developing brain and increased risk of being a victim of alcohol-related incidents (Lees et al., 2020, Conrod and Nikolaou, 2016).

Adolescence is a period of vital importance for the prevention of alcohol use and mental disorders (Sawyer et al., 2018, Kleinert and Horton, 2016). Throughout adolescence, there is an increased susceptibility for the development of alcohol use problems and mental ill-health (Costello et al., 2011). Even small increases in mental health symptoms in adolescence can increase the likelihood of developing a mental disorder as an adult (Fergusson, 2005). Further, evidence suggests that early onset of alcohol use increases the risk of subsequent heavy alcohol use and comorbid mental health problems (Teesson, 2005, Liang and Chikritzhs, 2015, Silins et al., 2018). Nationally representative interviews in the US have estimated that 50 – 70% of adults with a mental disorder experienced a disorder in their youth, based on retrospective accounts (Costello et al., 2011, Kessler et al., 2005). However, mental disorders are often undetected and untreated in young people due to problems recognising mental health problems and barriers to help-seeking (ten Have et al., 2013, Thornicroft, 2012, Wang et al., 2007).

Unfortunately, the effectiveness of existing prevention programs for alcohol use and mental disorders among adolescents tends to be modest and they suffer from implementation barriers (Fazel et al., 2014). School-based prevention programs tend to be universal, meaning that those with low risk of problematic alcohol use and mental disorders are given the same intervention as those at higher risk. Further, prevention programs typically target single disorders, meaning that multiple programs would be required to make an impact. *Preventure* is the only evidence-based prevention program addressing shared risk factors for problematic alcohol use, internalising problems and externalising problems in schools (Teesson et al., 2017, Conrod et al., 2006, Conrod et al., 2008, Newton et al., 2016, Newton et al., 2019, Castellanos and Conrod, 2006). *Preventure* is selectively delivered to adolescents with one of four personality risk factors: anxiety sensitivity, hopelessness, sensation seeking, and impulsivity. While *Preventure* was designed as a substance use prevention program, the four personality risk factors have been found to predict internalising and externalising problems in addition to problematic alcohol use and illicit drug use (Newton et al., 2016 2016/02/01/;53:23–30., Castellanos-Ryan et al., 2013, Woicik et al., 2009).

The effectiveness of the *Preventure* program when delivered by external psychologists has been demonstrated in Canada and the United Kingdom (Conrod et al., 2006, Conrod et al., 2008, Conrod et al., 2010, Castellanos and Conrod, 2006). A recent Australian cluster RCT replicated these results, indicating successful adaptation of the *Preventure* program for students in Australia when led by psychologists; results showed that *Preventure* successfully reduced the uptake of alcohol, binge drinking and alcohol-related harms up to 36-months following the intervention (Teesson et al., 2017, Newton et al., 2016, Newton et al., 2019, Barrett et al., 2015), with effect sizes (in Cohen’s *d*) of 0.47, 0.65 and 0.54 respectively (Conrod, 2016), equating to a moderate effect. In addition, the Australian adaptation showed secondary effects for mental health outcomes, including anxiety and depressive symptoms, conduct problems and hyperactivity symptoms (Newton et al., 2019).

### Important next steps to advance prevention

1.1

Recent systematic reviews have highlighted a number of important areas for improving the evidence base on the prevention of alcohol use and mental disorders; a key recommendation is evaluating programs that target disorders with shared underlying vulnerabilities (Bennett et al., 2015, Stockings et al., 2016a, Stockings et al., 2016b). There is increasing evidence that *Preventure* is efficacious for internalising and externalising problems in addition to alcohol use (Newton et al., 2019, Castellanos and Conrod, 2006, Kelly et al., 2020, O'Leary-Barrett et al., 2013); strengthening this evidence base will address this gap in current prevention efforts.

Another important step in improving the field of prevention is to move from simply demonstrating efficacy to evaluating the translation and implementation of efficacious programs into wider use in the population (Gottfredson et al., 2015). Effectiveness trials seek to test whether the positive effects observed in efficacy trials are robust to variations to the intervention, population, setting, and other adaptations likely to occur when an intervention is implemented more broadly (Gottfredson et al., 2015). One UK trial shows evidence that a teacher-led delivery of *Preventure* demonstrated significant impacts on alcohol use and mental health outcomes, with effect sizes similar to those found when the intervention was delivered by external psychologists (O'Leary-Barrett et al., 2013, O'Leary-Barrett et al., 2010). The current study is an Australian-first trial to evaluate the effectiveness of the *Preventure* program when implemented by school staff in Australia. Confirming the effectiveness of the *Preventure* program when delivered by school staff will enhance the scalability of the program, by providing a more feasible delivery method for schools.

## Objectives

2

The main aim of the current study is to examine the effectiveness of *Preventure* in preventing the onset or escalation of alcohol use, internalising problems and externalising problems by targeting shared personality risk factors, when delivered by school staff (e.g. teachers, school counsellors) in Australia. It is hypothesised that compared to ‘high-risk’ students (i.e. those scoring one standard deviation above the population mean for one of the four personality risk factors) in control schools, ‘high-risk’ students in *Preventure* schools will show significantly reduced:i)Alcohol use (uptake, quantity and frequency, binge drinking), intentions to use alcohol, and alcohol-related harms;ii)Internalising problems (anxiety and depressive symptoms); andiii)Externalising problems (conduct problems and hyperactivity symptoms).

An additional aim of the study is to examine the implementation fidelity, feasibility and acceptability of the program when delivered by school staff.

## Methods and analysis

3

The School-led *Preventure* trial is a CONSORT-compliant cluster randomised controlled trial, to be conducted in 12 secondary schools in greater Sydney in NSW, Australia. Schools will be stratified by majority gender (i.e. >60% male or female) and randomised to either i) intervention (*Preventure*) or ii) control (health education as usual). Each condition will include 6 schools. *See*
Fig. 1.

**Fig. 1 f0005:**
[figure not shown]
Flowchart of planned recruitment, randomisation and assessment process for 2020–2022, Sydney, Australia.

### Inclusion criteria

3.1

Participants must be a Year 8 student (aged approximately 13 years) in a participating school at the time of randomisation and fluent in English. Teachers may exclude students at their discretion if they believe a student will not be able to undertake the program due to learning difficulties, or if they will be disruptive to other students. Any such students will be offered alternatives, such as one-on-one delivery. This will be recorded in staff fidelity measures.

Trial sites (schools) must:i)Be a secondary or combined primary and secondary school in greater Sydney, NSW; andii)Have school principal permission to participate in the trial.iii)Have at least 60 students enrolled in Year 8 at recruitment, to ensure there are sufficient group sizes to run the intervention.

### Intervention

3.2

Schools allocated to the *Preventure* intervention will identify students to participate in the intervention based on their scores on the Substance Use Risk Profile Scale (SURPS; Woicik et al., 2009). Students scoring greater than one standard deviation above the population mean, as determined in the previous Australian trial (Newton et al., 2016), on any one of the traits measured by the SURPS (anxiety sensitivity, hopelessness, sensation seeking and impulsivity) will be invited to participate in the intervention that corresponds to the personality trait on which they score furthest from the mean. These groups are mutually exclusive: students can only participate in one personality-matched group. Students with elevated scores on more than one subscale will be allocated to the personality group where they deviated most from the population mean, according to z scores. Based on previous trials and Australian norms (Newton et al., 2016), it is anticipated that approximately 40% of students will screen into the intervention, with approximately equal numbers in each of the four groups.

The *Preventure* intervention consists of two 90-minute sessions with small groups of students (approximately 4–8 students per group), led by a trained facilitator and co-facilitator. Aided by real life example scenarios, the sessions incorporate: i) psycho-education about the target personality style and associated maladaptive coping behaviours (e.g., avoidance, aggression, and alcohol use); ii) development of an individualised model of the physical, cognitive and behavioural components of typical responses; and iii) motivational enhancement, goal-setting and application of cognitive-behavioural skills to modify problematic reactions and behaviours. At the end of each session, staff involved in the program delivery will be asked to complete a short survey measuring their adherence to the intervention as a measure of fidelity. The intervention will be delivered in addition to the NSW state-mandated Health and Physical Education curriculum for all Year 8 students. This curriculum includes lessons on mental health and wellbeing and alcohol and other drugs. Information on the health education as usual lessons will be made available to the research team by school staff.

### School staff training and supervision

3.3

The facilitators and co-facilitators will include school staff, who will be trained according to the training protocol as described in O'Leary-Barrett et al. (2013). This includes a training workshop, followed by supervision to ensure adherence to the intervention. Supervision will include being observed by the trainer delivering the two 90-minute workshops for one personality type, with a group of students not included in the trial, and one hour of feedback from the trainer. Training and supervision can be delivered online if required due to Covid-19 restrictions. All facilitators will be provided with intervention manuals to assist in their delivery of the program (Table 1).

**Table 1 t0005:** Anticipated participant activities and assessment timeline for 2020–2022, Sydney, Australia.

Timing	September–December 2020	October 2020–March 2021	April–September 2021	October 2021–March 2022	January–July 2022
Participant					
Intervention staff	Training workshop + supervision	Preventure Intervention and intervention adherence survey	Staff survey		
Intervention students		1. Student baseline survey 2. Preventure intervention and feedback survey	Student survey 2: 6-month follow up	Student survey 3: 12-month follow up	
Control staff					Training workshop + supervision (offered)
Control students		Student baseline survey	Student survey 2: 6-month follow up	Student survey 3: 12-month follow up	

### Control condition

3.4

Control schools will implement health and physical education as usual. The Year 8 Health and Physical Education curriculum mandates that mental health and wellbeing, and alcohol and other drug content be implemented. At the end of the study control schools will be informed of the results of the trial and offered complimentary use of the intervention, including training in *Preventure* delivery.

### Outcomes

3.5

The primary outcomes are differences in the prevalence and/or means of ‘high-risk’ students in the intervention and control schools on alcohol use, internalising problems (anxiety and depressive symptoms) and externalising problems (conduct problems and hyperactivity symptoms), at 6- and 12-months post baseline. Specifically, it is hypothesised that ‘high-risk’ students in the intervention group will have lower prevalence/scores than ‘high-risk’ students in the control group, on the following primary outcome measures:i)Alcohol use

A series of questionnaires adapted from the School Health and Alcohol Harm Reduction Project ‘Patterns of Alcohol’ index (McBride et al., 2004) will be used to measure intention to try alcohol, any use of alcohol ever (at least a standard drink), the frequency and quantity of alcohol consumption in standard drinks in the past six months, and frequency of binge drinking (five or more standard drinks on one occasion) in the past six months. Alcohol-related harms will be measured with an abridged form of the Rutgers Alcohol Problem Index (RAPI) (White and Labouvie, 1989). The original scale shows high internal consistency with adolescent samples (White and Labouvie, 1989). These questions were used in the previous Australian trial of *Preventure* (Newton et al., 2016, Newton et al., 2012).ii)Internalising problems

The ‘Kessler 6′ scale (K6) (Kessler et al., 2002) will be used to assess psychological distress in the past month. The K6 shows high accuracy, consistency across samples, and specificity (Kessler et al., 2002). Depressive symptoms will be measured using the ‘Patient Health Questionnaire, modified for adolescents (PHQ-A) (Johnson et al., 2002), which demonstrates good sensitivity and specificity, diagnostic validity and accuracy (Johnson et al., 2002). Anxiety symptoms will be measured by the ‘Generalised Anxiety Disorder 7-item scale’ (GAD-7), which shows strong reliability and validity (Spitzer et al., 2006).iii)Externalising problems

The conduct problems and hyperactivity subscales of the Strengths and Difficulties Questionnaire (SDQ) (Goodman, 1997) will be used to assess externalising problems. These subscales have been confirmed with a five-factor structure demonstrating satisfactory reliability and validity, predicting an increased likelihood of psychopathology (Goodman, 2001).

Secondary effects of Preventure will be explored for:•Social anxiety [adapted from the Mini-Social Phobia Inventory (Mini-SPIN) (Connor et al., 2000)] and panic attacks (adapted from the Panic Attack Questionnaire (Norton et al., 2008);•Other drug use (use of tobacco, e-cigarettes, and cannabis in the past six months);•Bullying (adapted version of the Olweus Bully/Victim Questionnaire (Olweus, 1996);•Emotion regulation (The Difficulties in Emotion Regulation Scale (Kaufman et al., 2016);•School engagement (The Hemingway Measure of Adolescent Connectedness (Karcher and Lee, 2002));•Quality of life (Satisfaction with Life Scale – Child version (Gadermann et al., 2010); and•Self-compassion (Self-compassion scale: Short-form (Raes et al., 2011).

Implementation acceptability, feasibility, and fidelity outcomes

The following outcomes will be used to inform efforts to scale-up the delivery of *Preventure* across Australia.•School staff-perceived feasibility and acceptability of delivering the *Preventure* intervention. Questions were developed for the trial using the RE-AIM framework (Glasgow et al., 1999) and seek information as to the perceived reach, effectiveness, adoption, implementation and maintenance of *Preventure* by school staff.•Stakeholder views and an indication of any challenges or barriers associated with delivery of *Preventure* and selective prevention more broadly.•Student feedback on the intervention, collected through a mix of open and closed questions about what they liked/disliked about the program•Staff implementation fidelity (i.e. adherence to the intervention), collected via a self-report form completed by the main facilitator and a report made by the co-facilitator, assessing which parts of the intervention were covered, whether the facilitator made any changes to the intervention and the facilitator’s use of counselling techniques.

A range of other measures will also be included to describe the sample and explore the relationships between these measures and the primary outcomes:•Demographics (age, gender, sex at birth, country of birth, grades at school, truancy, and a proxy for family socio-economic status used in the HBSC study, which includes items such as the number of cars and computers in the family home (Currie et al., 1997);•Age of first alcohol consumption, maximum number of standard drinks consumed on one occasion and perceived proportion of students’ friends who drink alcohol (adapted from the School Health and Alcohol Harm Reduction Project ‘Patterns of Alcohol’ index (McBride et al., 2004);•Other drug use (ecstasy, methamphetamine);•Social contact and support (Items used from the National Survey on Mental Health (Slade et al., 2007);•Interpersonal emotion regulation (a shortened version of the Interpersonal Regulation Questionnaire (Williams et al., 2018);•Emotional neglect (adapted from the CDC-Kaiser Permanente Adverse Childhood Experiences Study (Felitti et al., 1998);•Relationship with a parent/guardian (The Parental Bonding Instrument (Parker et al., 1979);•Climate change anxiety (adapted from the Anticipatory Traumatic Reaction feelings subscale (Hopwood et al., 2017);•Covid-19 exposure and impact (sourced from the Australian National Covid-19 mental health, behaviour and risk communication survey (Australian National University, 2020), and the Distress Questionnaire-5 (Batterham et al., 2016).

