### Statistical methods

3.10

Intention-to-treat analyses will be carried out for all primary and secondary outcomes, among the ‘high-risk’ students. Baseline equivalence and attrition between groups will be examined using single-level analyses; one-way analyses of variance (normally distributed data), chi-squared analyses (binominal data), and Mann-Whitney U-tests (non-normally distributed data). To examine intervention by time interaction effects, mixed effects regression will be used due to the multi-level nature of the data (students nested within schools). Hypothesised intervention effects on alcohol use, internalising problems and externalising problems will be examined using mixed effects linear regression analysis (continuous data) and mixed effects logistic regression analysis (categorical data). Missing data will be handled by full information maximum likelihood, in accordance with the intention-to-treat principle, which includes all randomised participants. Data from the school staff survey will be predominantly descriptive.

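### The intervention-by-time logistic model, applied to lifetime ever-use in all high-risk students, estimates a diluted change in prevalence odds and not the uptake effect that is hypothesised

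*Protocol article*

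**What the plan says.** All references are to the protocol article.

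- **Objectives (section 2).** The aim includes "preventing the onset or escalation of alcohol use". The first hypothesis is a reduction in "Alcohol use (uptake, quantity and frequency, binge drinking), intentions to use alcohol, and alcohol-related harms". Uptake is the first alcohol effect named.
- **Outcomes (3.5).** Among the primary alcohol measures is "any use of alcohol ever (at least a standard drink", a lifetime yes/no item. The section opens with "The primary outcomes are differences in the prevalence and/or means of" high-risk students in the two arms, at 6 and 12 months.
- **Statistical methods (3.10).** "To examine intervention by time interaction effects, mixed effects regression will be used", with students nested within schools given as the reason. Categorical outcomes get "mixed effects logistic regression analysis (categorical data". The analysis set is the high-risk students. Ever-use has no separate rule, no restriction to baseline never-users and no onset model.
- **Data collection (3.9).** Surveys take place at baseline, before the intervention, and at 6 and 12 months.

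**The concern.** An intervention-by-time interaction suits an outcome that can rise or fall within a student. Lifetime use cannot. If answers are truthful, only four patterns occur over the three surveys: 000, 001, 011 and 111. A student who is yes at baseline is yes throughout and cannot show uptake. That student still counts in the prevalence at each wave and pulls the arms together on the odds scale.

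Two things follow. The coefficient answers a different question from the hypothesis, and the test can be much less sensitive than a direct comparison of new use. How much less depends on how the repeated answers within a student are modelled. Section 3.10 names only the school level.

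At stake is the first-named alcohol effect. A real reduction in onset could be reported as a small, non-significant interaction.

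**Working it through.** **The plan's own figures.** None is given for ever-use. The 280 students in section 3.6 refer to a standardised mean difference of 0.3, not to a binary item, and are not tested here. The recruitment target reproduces: 12 × 75 × 0.40 = 360 high-risk students, or 180 per arm.

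**Assumptions (not in the article).** Baseline ever-use p0 = 0.15 in both arms; new use per six months among never-users 12% (control) and 7% (intervention); no school effect, no attrition, consistent answers, two-sided 5% test.

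**Step 1: what each contrast estimates**
- New use by 12 months among never-users: control 1 − 0.88² = 0.2256; intervention 1 − 0.93² = 0.1351. OR = (0.1351/0.8649)/(0.2256/0.7744) = 0.54, log OR −0.623.
- Ever-use at 12 months in all students, p0 + (1 − p0) × new use: control 0.15 + 0.85 × 0.2256 = 0.3418; intervention 0.15 + 0.85 × 0.1351 = 0.2648. OR = 0.69, log OR −0.366.
- Baseline prevalence is equal, so the 12-month-versus-baseline interaction is also −0.366.

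**Step 2: comparison among never-users**
- n = 180 × 0.85 = 153 per arm. Variance = 1/(153 × 0.2256 × 0.7744) + 1/(153 × 0.1351 × 0.8649) = 0.0933; SE 0.306.
- Power = Φ(0.623/0.306 − 1.96) ≈ 0.53.

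**Step 3: interaction with school nesting only**
- Repeated answers count as independent. Assumed variance = Σ 1/(n p q) over two arms and two waves = 0.0871 + 0.0247 + 0.0285 = 0.1404; SE 0.375.
- The two answers of one student have covariance p0(1 − p12), where p12 is 12-month prevalence. On the logit scale this is 1/(n(1 − p0)p12): 0.0191 (control) and 0.0247 (intervention).
- True variance = 0.1404 − 2 × (0.0191 + 0.0247) = 0.0528; SE 0.230.
- Power = Φ((0.366 − 1.96 × 0.375)/0.230) ≈ 0.05.
- With both arms at control rates, the assumed variance is 0.1365 and the true variance 0.0600 (ratio 0.44), giving type I error of about 0.3% instead of 5%.

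**Step 4: interaction with correct within-student covariance**
- Power = Φ(0.366/0.230 − 1.96) = 0.356, about 35%.

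**Step 5: prevalence difference at 12 months, all students (section 3.5 reading)**
- SE = √(0.0247 + 0.0285) = 0.231; power about 0.35.

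Simulation under the same assumptions gave 5%, 53% and 35% for steps 2, 3 and 5 in the order 3, 2, 5.

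**Step 6: range of baseline ever-use, same formulas and new-use rates**

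| Baseline ever-use | Interaction OR (never-user OR 0.54) | Power, school only | Power, correct covariance | Power, never-users |
|---|---|---|---|---|
| 5% | 0.60 | 10% | 21% | 58% |
| 15% | 0.69 | 5% | 36% | 53% |
| 30% | 0.77 | 1% | 39% | 46% |

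A wider grid used 140 per arm, baseline use 5–30% and control 12-month uptake 10–30%. Effects were converted by OR = exp(−dπ/√3): 0.58 at d = 0.3, and 0.43 at d = 0.47, the earlier uptake effect cited in the Introduction.

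| Effect | School only | Correct covariance | Never-users |
|---|---|---|---|
| d = 0.3 | 0.00–0.08 | 0.12–0.30 | 0.17–0.47 |
| d = 0.47 | 0.00–0.18 | 0.22–0.58 | 0.30–0.80 |

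**Step 7: adding a student random intercept (60 simulated trials per scenario)**
- Fully consistent answers: the intercept SD reached its cap of 60 in 83–100% of fits, and interaction coefficients were about −14 to −26 against true log ORs of −0.54 to −0.85. The likelihood-ratio test still kept about half the never-user power.
- With 5–15% of ever-users denying use at a given wave, the SD was finite, about 4.5 to 8.

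**The case against.** A reader might infer that the stated model must either break down or lose nearly all its power. The article does not support that.

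- Section 3.10 gives students within schools as the reason for mixed models. It is not a full random-effects specification, and an analysis plan may add a student level or a suitable covariance. The 5% figure belongs to the school-only reading alone.
- Divergence needs perfectly consistent answers. The Strengths and limitations section accepts that self-report may be biased, and modest retraction makes the fit finite.
- Section 3.5 defines the primary outcomes as differences in prevalence at follow-up. For ever-use that is a valid between-arm contrast. Section 3.10 can also be read as two sentences, with only the first naming the interaction.
- Adjusting follow-up prevalence for baseline use would also serve.
- Section 3.10 commits to intention to treat, and restriction drops some randomised students.

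The first three points limit the size of the claim. They do not rescue the target, because under every covariance structure the interaction in all students is not uptake. The prevalence contrast is diluted too, and it is not the interaction, so 3.5 and 3.10 need reconciling for this item. With consistent answers, baseline adjustment reduces to the never-user comparison. On intention to treat, never-use at baseline is recorded before the intervention, on the same survey that defines the high-risk set. Baseline ever-users cannot contribute to uptake in either arm.

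**Conclusion.** The point holds in limited form. The analysis stated for lifetime ever-use does not estimate the hypothesised effect, and this is a mismatch in what the article fixes, not detail left to another document. Under the main assumed rates the odds ratio moves from 0.54 to about 0.69. Power falls from about 53% to about 35% with correct within-student covariance, or to about 5% with school nesting only. These sizes rest on assumed alcohol rates, no school effect and no attrition. The ranges in the working show that the gap can be small or large. Breakdown of the model is possible but not certain. One item among several alcohol measures is affected. It should be corrected before analysis.

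**What to change.** In sections 3.5 and 3.10:

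1. Define uptake as the first report of at least one standard drink among high-risk students who report never use at baseline.
2. Analyse it by 12 months with a logistic model with a school random intercept, or with a discrete-time hazard model over the 6- and 12-month surveys. Use this in place of the intervention-by-time term for this item.
3. State a rule for students who later retract a report of use.
4. If wanted, keep follow-up prevalence in all high-risk students as a supporting analysis, labelled as such.

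**Cost.** Wording only, with no new data. The denominator shrinks (153 instead of 180 per arm at 15% baseline use). The change does not bring this item to 80% power at modest effects: it reaches 0.17–0.47 at d = 0.3 over the assumed ranges with 140 per arm. The write-up should say so.
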